#### Medical Record Review (Research Abstracted)

The researcher will review the participant’s medical record and document any pain-related medication (name and dosage) that the participant used prior to the laser procedure. Demographics and procedure information recorded will include the date of birth, sex, race, ethnicity, and dermatologic variables (laser type, diagnosis, lesion size, lesion type, and lesion location).

### Outcomes

#### Feasibility Outcomes

The feasibility of using VR during outpatient laser procedures will be evaluated by the proportion (%) of patients screened who are eligible to be approached, those who consent to the study, and those who complete both study visits. This will be tracked in our screening log and analyzed periodically throughout the study for funding reporting. Adverse events, including simulator sickness, will also be used to evaluate feasibility (see “Adverse Events and Oversight” section for specifics). The threshold for scaling up this study is no serious adverse events reported, less than 10% loss to follow-up due to the VR, and greater than 80% of both patients and nurses being satisfied with the intervention. Clinical loss to follow-up will not be counted in this measure. There is no predefined proportion for recruitment and consent, but these outcomes will be used to determine the possible sample size.

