## Methods

### Trial Design

We will conduct a prospective, 2-group crossover RCT with a 1:1 allocation ratio to either the intervention (VR-PAT gameplay) or the control (VR headset turned off) for the first laser appointment. Participants will crossover to the opposite group at their second laser appointment. Pain, anxiety, and VR engagement (for those in the intervention group) will be assessed after each research appointment, spaced approximately 6 to 8 weeks apart. The findings will be reported based on the CONSORT (Consolidated Standards of Reporting Trials) guidelines. This protocol is reported in accordance with the SPIRIT (Standard Protocol Items: Recommendations for Interventional Trials) guidelines (Checklist 1).

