### Randomization and Blinding

A block randomization scheme with a block size of 4 will allocate participants to 1 of the 2 intervention sequences (VR-PAT followed by control or control followed by VR-PAT) at a 1:1 ratio without stratification. We chose a block randomization strategy to avoid imbalances in allocation to the intervention at the first visit in case we were unable to recruit our planned sample. The randomization scheme was developed and uploaded to a study-specific REDCap (Research Electronic Data Capture; Vanderbilt University) project by the project manager. Study participants are randomized into intervention sequences after signing consent and completing the baseline survey. Research recruiters and participants are not aware of the intervention assignment until the participant is randomized in REDCap.

We cannot blind the participants or the clinical team to the assigned intervention since the headset will either be turned on or off. The researcher who randomized the participant and observed the laser procedure will not be blinded, but a second researcher, who is blinded to the intervention group, will collect pain ratings and anxiety post procedure. The second researcher will wait in a different room during randomization and the laser procedure, and the first researcher will remind the participant at the end of the laser procedure to keep their group a secret until they are asked. The study biostatistician will also be blinded to the intervention group while performing analyses on the primary outcome. The data will be blinded by removing labels such as “VR” and “Control” and replacing them with unidentifiable letters (eg, “A” and “B”). The biostatistician will need to be unblinded for secondary outcomes, as only participants in the intervention group will answer the VR experience questions.

The blinded researcher will need to be unblinded after pain and anxiety ratings are obtained, as those in the control environment will not be able to answer the VR experience questions. The researcher will become unblinded by asking participants whether they played the game. The biostatistician will also be unblinded for full analyses by being provided with the full dataset, including complete data labels and VR questions. This unblinding will take place after the primary outcome analysis has been completed.

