#### Participant Data (Self-Reported)

Prior to randomization, participants will report their prior video game experience, including the type of video games played, frequency, and favorite games. Before the laser procedure, all participants (control and intervention visits) will self-report their anxiety state using the State-Trait Anxiety Inventory for Children [32] (ratings ranging from “not at all” to “very much”) and their current anxiety using the Numeric Rating Scale (NRS; 0‐10) [33]. After the procedure, the participants will answer the remaining survey questions assessing overall pain score (NRS 0‐10) [34,35], worst pain score (NRS 0‐10), time spent thinking about pain (NRS 0‐10), length of the procedure (in minutes), and anxiety during the laser procedure (NRS 0‐10). Those playing the VR-PAT game will report their experience with the VR game (degree of realism, fun, engagement, and satisfaction; NRS 0-10) and respond to qualitative questions about their preferences with the VR-PAT. Participants will also be asked to report any simulator sickness associated with the VR game and whether they would want to use the VR again for future laser visits outside of research. These data will be collected at each of the 2 laser procedure study visits.

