#### Observed Measures (Research Collected)

The Modified Yale Preoperative Anxiety Scale (mYPAS) [37] will be assessed at each laser procedure before entering the treatment room, before the procedure begins, and immediately following the procedure. This is a 5-item scale, with a score of more than 30 indicating anxiety. During the procedure, the researcher will document the start and stop times of the laser procedure, the start and stop times of the VR (if applicable), whether the participant declined to use the VR-PAT, and the number of voluntary interruptions of the VR-PAT.

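### The patient-based criteria for scaling up do not register participants who decline VR but stay in the trial, and the loss limit can detect loss after VR use only in the VR-first half

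*Protocol article*

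**What the plan says.** The rule is in the protocol article under Feasibility Outcomes. Its first two criteria are "The threshold for scaling up this study is no serious adverse events reported, less than 10% loss to follow-up due to the VR". The third is "greater than 80% of both patients and nurses being satisfied with the intervention". On the loss criterion the article adds: "Clinical loss to follow-up will not be counted in this measure". No denominator is given for either percentage.

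Observed Measures lists what the researcher in the room records, including "whether the participant declined to use the VR-PAT, and the number of voluntary interruptions of the VR-PAT", together with start and stop times for the laser and for VR. Participant Timeline lists similar items. None of them appears in the rule.

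On who rates satisfaction, Participant Data says: "Those playing the VR-PAT game will report their experience with the VR game", and satisfaction is one of those items. Randomization and Blinding explains how the interviewer gets to them: "The researcher will become unblinded by asking participants whether they played the game". Participant Timeline says something different, namely that both groups are asked about satisfaction with the game.

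Nurses answer two yes/no items, on helpfulness and ease of use, at the intervention visit (Secondary Outcomes). Trial Design gives the order of exposure: "Participants will crossover to the opposite group at their second laser appointment". Allocation to the two sequences is 1:1 in blocks of 4.

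**The concern.** The trial asks whether children and young people will use a headset game during laser treatment. The most direct evidence is whether they accept it and keep it on. The rule instead uses loss between two visits and satisfaction among raters.

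A participant who says no to the game but returns as scheduled adds nothing to the loss count. On the wording of Participant Data and of Randomization and Blinding, that person also leaves both the numerator and the denominator of patient satisfaction. The satisfaction figure then describes a self-selected group, those willing to play.

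The loss criterion has a separate weakness. Loss after using VR needs a later visit to be missed. Participants who have VR second have no later study visit.

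The abstract says the results will inform a large multisite study, so a favourable reading based on players alone would carry forward into its planning.

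**Working it through.** The 10% and 80% limits are chosen values and the sample of 40 was set by budget and patient volume, so there is no derivation to reproduce. The reported flow is consistent: 44 − 40 = 4 non-completers = 3 (laser treatment discontinued) + 1 (no interest in the VR game).

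**Patient satisfaction when some decline (illustration, 40 VR visits).** Assume 10 decline, all 40 attend both visits, and 26 of the 30 players are satisfied.
- VR-related loss: 0/40 = 0%, which meets the limit.
- Satisfied among players: 26/30 = 86.7%, which meets the limit.
- Used VR and satisfied, among all 40: 26/40 = 65%, which does not.

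As a more extreme case, suppose 20 decline and 17 of 20 players are satisfied. Players give 17/20 = 85%, against 17/40 = 42.5% of all.

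**If decliners count as not satisfied.** More than 80% of 40 needs at least 33 satisfied (33/40 = 82.5%; 32/40 = 80.0% is not above 80%). At most 40 − 33 = 7 could decline (7/40 = 17.5%), and then only if every player were satisfied.

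**Nurse criterion in the same illustration.** If nurses answered no at the 10 declined visits, at most 30/40 = 75% would be positive and the rule would fail. If they answered on other grounds, it might pass. The article does not say how nurses answer when the game was declined.

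**Loss criterion.** Assume an exact 1:1 split, all participants as denominator, and no control-first participant leaving because of VR.
- N = 40: the largest passing count is 3 (3/40 = 7.5%; 4/40 = 10.0% is not below 10%). Among 20 VR-first participants this is 3/20 = 15.0%.
- N = 44 (11 blocks of 4, so 22 per sequence): the largest passing count is 4 (4/44 = 9.1%). Among 22 this is 4/22 = 18.2%.
- With VR-first participants as denominator, the largest passing counts are 1/20 = 5.0% and 2/22 = 9.1%.

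The chance of passing is P(X ≤ m) with X binomial(n, p), where n is the size of the VR-first half and m the largest passing count. For a true post-VR loss of p = 20%:

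| | All participants | VR-first only |
|---|---|---|
| N = 40 (n = 20) | m = 3: 0.41 | m = 1: 0.07 |
| N = 44 (n = 22) | m = 4: 0.54 | m = 2: 0.15 |

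**Reported loss.** One VR-related loss gives 1/44 = 2.3%, or 1/41 = 2.4% without the three clinical losses. It is at most 1/22 = 4.5%, if that participant was VR-first.

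**The case against.** Several points against the concern stand.

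- A reader might infer that the rule is also blind to participants who abandon VR. The article does not support that. Someone who starts and stops has played, can rate satisfaction low and is asked whether the game made them feel unwell. A bad experience at the last visit can reach the rule the same way. Abandonment is therefore only partly missed.
- A reader might infer that a widely declined device would pass the whole rule. That is not shown either. Nurses rate at the intervention visit with no restriction to players, and their criterion could fail the rule.
- A reader might take the dilution of the loss limit as a fact. It depends on an all-participant denominator that the article does not state and that the full protocol may settle. Control-first participants can also leave in anticipation of VR. The sequence of the one reported VR-related loss is not given.
- Participant Timeline has both groups asked about satisfaction, and the rule says patients, not players. Data Analysis also promises analysis by assignment whatever the compliance. This makes the players-only denominator a matter of conflicting text. It does not remove the problem: analysis by assignment cannot supply a rating that was never taken, so a counting rule for decliners is still needed.
- Nothing reported suggests heavy refusal. Results has 40 patients using VR, although that may mean assigned to it, and counts of declined or interrupted use are not given.
- Feasibility is also described by eligibility, consent, completion and adverse events, so the threshold is not the only evidence.

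**Conclusion.** The concern holds for the patient-based criteria. A participant who declines VR and stays is not a loss and, on two of the three passages about who is asked, is not a rater, although the refusal itself is recorded. In the illustration this is the difference between 87% and 65%. The illustration assumes 10 refusals in 40 and a players-only denominator. It is not an estimate of what happened.

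For the loss criterion, the structural part is certain: loss after VR use can occur only in the VR-first half. Its size, 15% to 18% tolerated in that half, is conditional on an all-participant denominator and on no VR-related loss in the control-first half.

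The article gives no ground for concluding that this trial's loss result is wrong, since the single VR-related loss is below 10% on every denominator. Acceptance of VR cannot be judged from the article.

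**What to change.** - Compute the patient satisfaction criterion over all participants who reach the VR visit, and count those who declined as not satisfied.
- Reconcile Participant Timeline with Participant Data and with Randomization and Blinding on who is asked about satisfaction with the game.
- Beside the threshold, report the proportion who declined VR or stopped it for a VR-related reason, among all assigned to it.
- Report VR-related loss by sequence and state its denominator.
- Keep the 10% and 80% limits, and label these additions as made after data collection, which ended in November 2025.

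Replacing the loss criterion with a broader failure definition at the same 10% is not needed. At this stage it would be a new criterion without a derivation.

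The cost is a few sentences and a tabulation of data already recorded. The downside is that the feasibility figure may look less favourable.

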#### Primary Outcomes

Difference in self-reported worst pain, average pain, and time spent thinking about pain (NRS 0 [min]−10 [max]) between VR-PAT and control visits. These questions are asked at each visit and will be compared between the intervention and control visits.

Change in procedural anxiety (mYPAS observed by the researcher, 23.33 [min]−100 [max], with higher scores denoting higher levels of anxiety) is assessed at 3 time points: prior to entering the procedure room, prior to the procedure, and immediately following the procedure for each laser procedure. These differences will be compared before and after the procedure, as well as between the intervention and control visits.

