**Methods:**

A total of 40 patients requiring outpatient laser therapy for at least 2 sessions will be recruited from a pediatric hospital in the Midwestern United States for this crossover randomized, 2-arm clinical trial. During the first laser visit, the participants will be randomly assigned to either play the VR-PAT game during their procedure or wear the headset with a dark screen. Participants will answer questions about their pain (Numeric Rating Scale 0‐10), anxiety (State-Trait Anxiety Inventory for Children, Numeric Rating Scale 0‐10, and Modified Yale Preoperative Anxiety Scale), and pain medication usage. Those playing the VR-PAT will report simulator sickness symptoms and their experience playing the game. At their second laser visit, participants will cross over to the opposite intervention. The primary outcomes are the differences in self-reported pain and anxiety between the 2 interventions. Feasibility outcomes include the proportion of screened patients who were eligible, have given consent, and completed both visits, as well as adverse events reported. To evaluate the efficacy of pain reduction, composite pain scores, and pain medication usage will be calculated for each laser visit. To evaluate the efficacy of anxiety reduction, the change in Modified Yale Preoperative Anxiety Scale scores will be compared between control and VR groups at each visit using the Wilcoxon rank sum tests. All statistical analyses will follow the intention-to-treat principle with regard to intervention assignment at each visit.

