### Sample Size

Since this is a pilot study, the focus of the statistical analysis will be on estimating the effect sizes of VR-PAT and their 95% CI, as well as the variances of the outcome measures. These findings will facilitate sample size calculations and study power estimates for future larger-scale randomized trials. We decided on a sample of 40 participants and 2 research visits based on the grant budget and the patient volume for the 1 dermatologist collaborating on this study.

Across acute pain studies, clinically meaningful improvements are generally larger than a 1-point change on the NRS 0‐10, with systematic review evidence suggesting minimum clinically important differences of approximately 13% to 36% reduction, with a median of 23% (IQR 18%-36%), corresponding to roughly 1.4‐2.3 points on the NRS [38,39].

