### Data Analysis

To achieve aim 1, composite scores will be calculated for each laser procedure, encompassing the pain score, pain medication use during the procedure, and whether rescue medication was used. The rationale for choosing the composite score as the outcome is that prior researchers have shown a significantly high positive relationship between pain medication use and self-reported pain scores [40]. From a clinical perspective, pain scores alone are influenced by the patients’ actual opioid use and may not fully reflect the treatment benefit of VR [41]. The composite score approach, therefore, provides a single, patient-centered outcome that represents overall analgesic benefit, aligning with the goal of achieving adequate pain control while minimizing opioid exposure. In our analysis, we will apply the rank-based approach by Dai et al [40] to assign weights to pain and medication use, reflecting their complementary clinical importance as measures of pain reduction [41]. In the primary analysis, the composite scores from the laser procedure with VR will be compared to those from the procedure with standard care (ie, control) using paired 1-tailed *t* tests or the Wilcoxon signed rank tests (depending on the distribution of the composite scores) due to the cross-over design. The clinical effect size will be the mean difference (if paired *t* tests are used) or median difference (if Wilcoxon signed rank tests are used) in the composite score between VR and control procedures. The SD of the difference will also be calculated.

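### The listed primary pain outcomes and the declared primary analysis name different variables, so the primary pain result is not fixed

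*Protocol article*

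**What the plan says.** **Abstract, Methods.** "The primary outcomes are the differences in self-reported pain and anxiety between the 2 interventions". The composite appears there only as an efficacy measure: "To evaluate the efficacy of pain reduction, composite pain scores, and pain medication usage will be calculated for each laser visit".

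**Outcomes, Primary Outcomes.** For pain: "Difference in self-reported worst pain, average pain, and time spent thinking about pain", followed by "These questions are asked at each visit and will be compared between the intervention and control visits". For anxiety: "Change in procedural anxiety (mYPAS observed by the researcher", measured at three time points per visit, with the statement that "These differences will be compared before and after the procedure, as well as between the intervention and control visits". The composite is in neither the primary nor the secondary list.

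**Data Analysis.** "In the primary analysis, the composite scores from the laser procedure with VR will be compared" with the control procedure by a one-tailed paired test. The composite combines a pain score, medication use and rescue use. The mixed models and the fallback for carryover also use the composite. For mYPAS, the first procedure has two between-group contrasts of change (T0 to T1 and T0 to T2). The second procedure has between-group comparisons of scores at T0 and T1 only.

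**Sample Size.** The trial is a pilot focused on effect sizes, 95% CIs and variances. The clinical benchmark is in NRS points: "clinically meaningful improvements are generally larger than a 1-point change on the NRS", with a range of roughly 1.4 to 2.3 points.

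**Randomization and Blinding.** The biostatistician works with coded group labels for the primary outcome, in the singular, and is unblinded once that analysis is complete.

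**The concern.** The outcomes section and the analysis section disagree about what the primary pain variable is. A reader of the first expects three NRS differences. A reader of the second expects one composite difference. Neither section ranks the candidates. Three things depend on the answer.

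- **The headline.** Data collection has ended and analysis is under way (Results). Any of four pain variables could later be presented as primary with some textual support.
- **The blinding.** Only the primary outcome is sure to be analysed under coded labels. If that means the composite, the three listed NRS outcomes may be analysed unblinded.
- **The pilot's product.** The next trial needs an effect size and SD on a defined scale. Data Analysis specifies these for the composite, while the quoted clinical benchmark is on the NRS.

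**Working it through.** The plan states no alpha, power or error rate, so it has no figure to reproduce. The main check is a comparison of outcomes with analyses.

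| Variable | Listed as an outcome? | Analysis stated in Data Analysis? |
|---|---|---|
| Worst pain, NRS | Primary | None of its own |
| Average pain, NRS | Primary | None of its own |
| Time thinking about pain, NRS | Primary | None |
| Composite (pain score, medication, rescue) | No | Yes, called the primary analysis; also the mixed models and carryover fallback |
| mYPAS | Primary | Yes, but with a different contrast |

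**The composite's pain item.** Participant Data (Self-Reported) collects both an overall and a worst pain score. Data Analysis refers to a single pain score without saying which, so the composite has at least two possible versions. The average pain of Primary Outcomes is presumably the overall score, but the article does not say so.

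**mYPAS.** Primary Outcomes defines a comparison between intervention and control visits, which in a crossover is a within-participant contrast. Data Analysis compares the two groups separately at each procedure. At the second procedure it uses scores instead of changes and leaves out T2, although T2 is measured there. The Abstract gives a third version: changes compared between groups at each visit.

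**How much freedom this leaves (illustration).**

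Inputs: k = 4 candidate pain variables (three NRS items plus the composite). One-sided per-test alpha is assumed to be 0.05 or 0.025.

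If the tests were independent, P(at least one false positive) = 1 − (1 − alpha)^k:

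- alpha 0.05: 1 − 0.95^4 = 1 − 0.8145 = 0.185
- alpha 0.025: 1 − 0.975^4 = 1 − 0.9037 = 0.096

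The four variables come from the same patient at the same visits, so they will be correlated. For a common correlation r, one million sets of four statistics were simulated as X_j = √r·C + √(1 − r)·E_j, with C and E_j independent standard normal. The result is the share of sets whose largest value exceeds the one-sided critical value:

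| r | alpha 0.05 | alpha 0.025 |
|---|---|---|
| 0 (formula) | 18.5% | 9.6% |
| 0.5 | 14.5% | 7.8% |
| 0.7 | 12.0% | 6.5% |
| 0.9 | 8.8% | 4.7% |

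With one named primary pain variable, the figure is the per-test alpha itself. The planned sample of 40 would not change, because it rests on budget and patient volume.

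**The case against.** The strongest reply is that this is a labelling mismatch in a small, estimation-focused pilot. Data Analysis does name one primary analysis for aim 1 and gives a reason for it: pain scores alone are affected by medication use. The Abstract discloses the composite. Primary Outcomes promises a between-visit comparison of the NRS items, and the missing test could sit in a fuller plan. Coded labels limit choosing a result by its direction. All of this stands, and it lowers the severity. It does not remove the contradiction, which lies between two sections of the same article. Coded labels also cannot settle which variable is primary.

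Four stronger readings are tempting but not supported.

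- **That none of the listed primary outcomes is analysed.** mYPAS has contrasts, tests, an effect measure and bootstrap limits, and a pain score enters the composite.
- **That the false-positive risk is about a third.** Adding the four mYPAS contrasts gives 1 − 0.95^8 = 0.337. This needs eight independent tests at an unstated alpha and merges pain with anxiety, in a trial that puts estimation first.
- **That no variance will be available for the NRS items.** Sample Size promises variances of the outcome measures, and these items are listed outcomes. What is missing is their stated analysis.
- **That worst pain must be primary because it is listed first.** The order of a list is no reason, and this would override the stated rationale for the composite after data collection has ended.

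The Abstract's wording on anxiety is a smaller matter. The adjective self-reported may apply to pain only, but it can also be read as covering anxiety, whereas mYPAS is rated by a researcher.

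**Conclusion.** The point holds in limited form. The three NRS pain items listed as primary have no stated test or effect measure, and the primary analysis uses an unlisted composite with an unspecified pain item. mYPAS is analysed, but not by the contrast that its outcome definition gives. The primary pain result is therefore open to choice. The size is about 9% to 15% for at least one false positive among four pain variables at correlations of 0.9 to 0.5, with 18.5% as the independence limit. This assumes 5% one-sided per test; at 2.5% the corresponding figures are 4.7% to 7.8%, and 9.6%. The correlations are also assumed. Because the trial is a pilot and its primary outcome is analysed under coded labels, this should be fixed but does not undermine the design.

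**What to change.** Before the blinded primary analysis, or with open disclosure if unblinding has occurred:

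1. Make the Abstract, Primary Outcomes and Data Analysis name the same single primary pain variable. Either the composite, with its pain item fixed and the composite listed under Outcomes, or one NRS item would resolve the conflict.
2. Label the remaining pain variables secondary. Analyse each NRS item as the paired VR-minus-control difference in points, with a 95% CI and the SD of the difference, so that it can be read against the 1.4 to 2.3 point benchmark.
3. Analyse mYPAS as the between-visit contrast given in Primary Outcomes, and describe it in the Abstract as observer-rated.
4. State which of these analyses are completed before the biostatistician is unblinded.

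The cost is a change of wording and a few additional paired estimates from data already collected. The drawback is that some outcomes lose primary status. Because data collection has ended, the date of and reason for the choice should be recorded.
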